## Abstract

**Background:**

Obesity is mainly attributed to environmental factors. In developed countries, the time spent on physical activity tasks is decreasing, whereas sedentary behaviour patterns are increasing.

The purpose of the intervention is to evaluate the effectiveness of an intensive family-based behavioural multi-component intervention (Nereu programme) and compared it to counselling intervention such as a health centre intervention programme for the management of children’s obesity.

**Methods/**Design**:**

The study design is a randomized controlled multicenter clinical trial using two types of interventions: Nereu and Counselling. The Nereu programme is an 8-month intensive family-based multi-component behavioural intervention. This programme is based on a multidisciplinary intervention consisting of 4 components: physical activity sessions for children, family theoretical and practical sessions for parents, behaviour strategy sessions involving both, parents and children, and lastly, weekend extra activities for all. Counselling is offered to the family in the form of a monthly physical health and eating habits session. Participants will be recruited according the following criteria: 6 to 12 year-old-children, referred from their paediatricians due to overweight or obesity according the International Obesity Task Force criteria and with a sedentary profile (less than 2 hours per week of physical activity), they must live in or near the municipality of Lleida (Spain) and their healthcare paediatric unit must have previously accepted to cooperate with this study. The following variables will be evaluated: a) cardiovascular risk factors (anthropometric parameters, blood test and blood pressure), b) sedentary and physical activity behaviour and dietary intake, c) psychological aspects d) health related quality of life (HRQOL), e) cost-effectiveness of the intervention in relation to HRQOL. These variables will be then be evaluated 4 times longitudinally: at baseline, at the end of the intervention (8 months later), 6 and 12 months after the intervention. We have considered necessary to recruit 100 children and divide them in 2 groups of 50 to detect the differences between the groups.

**Discussion:**

This trial will provide new evidence for the long-term effects of childhood obesity management, as well as help to know the impact of the present intervention as a health intervention tool for healthcare centres.

**Trial registration:**

ClinicalTrials.gov, NCT01878994

## Background

Obesity in children is one of the most important public health a problem in the 21st century, as it is has been voiced for years by the World Health Organization. It is considered the most common nutritional or metabolic disorder and the main non-contagious illness in developed countries. The National Health Survey in Spain [1], in its three last editions [2003, 2006, 2010], has shown a continuous increase in overweight [18.2- 18.7- 19.2%] and obesity percentages [8.5- 8.9- 9.4%], in children between 2 and 17 years old. More recently, the results of Aladinos’ study [2], indicated that 45.2% of children between 6 and 9.9 years of age are either obese or overweight.

Obesity is a complex and multifactorial cronical illness, with its origin in a behavioural and environmental interaction [3], leading to an imbalance between energy intake and expenditure [4]. It usually begins in childhood or adolescence and it is considered a risk factor for metabolic, cardiovascular and pulmonary diseases [5]. We need to take also into account the psychosocial problems of obese child [5] and their lower quality of life compared to their healthy-weight peers [6].

Due to its important health, social and psychological consequences [7], the prevention and treatment of childhood obesity has become one of the leading priorities of public health. It is critical to begin prevention during childhood as childhood obesity tends to persist into adulthood [7]; about 70% of obese children continue to be obese into their adulthood [8].

Connely et al. [9] consider that physical activity at moderate-to-high intensity is the principal factor to distinguish between effective and ineffective childhood obesity prevention programmes. However, in childhood obesity treatment programmes, performing physical activity 3 times per week was not enough to reduce adiposity [10-12]. According to Trinh [13], focusing treatment of childhood obesity only in physical activity is not enough, as its relationship to body mass index (BMI) is not clearly quantified.

Reviews from Atlantis [14], McGovern [15] and Spruijt-metz [16] have shown that 12% -14% of the programmes treating childhood obesity that include physical exercise have a positive effect on the amountof adiposity. Oude Luttikhuis et al. [17], after performing a systematic review on the interventions to treat obesity in children and youngsters, show that the most effective programmes are those which integrate different strategies in obesity management besides physical activity. They emphasize the value of family interventions involving physical activity, nutrition and behaviour. Furthermore, in a meta-analysis, Whitlock [18] adds that intervention effectiveness depends on the total length of the intervention, considering moderate (26–75 hours/intervention) to high (>75 hours/intervention) intensity interventions the most effective ones.

Thus, this increase on physical activity practice needs to be linked to changes in other important habits such as nutrition, psychological aspects and the behaviour of the nuclear family [17,19-21], the latter being even more necessary in pre-adolescent children [20,22].

These other factors can be responsible for obesity maintenance and one of the limiting factors in childhood obesity interventions.

Recent bibliographic reviews [7,14-18,21] show that this is a growing research field but there are still questions to resolve, such as the high percentage of incomplete follow-ups, which make it difficult to assess the long-term effectiveness of the programmes/interventions. In addition, paediatric units still lack effective tools to treat obesity in children. In this sense, the Nereu programme (NP) has been developed in order to give paediatric units a tool to help them in the management obesity long-term.

The aim of this study is to evaluate the effectiveness of an intensive family-based behavioural multi-component intervention (NP) compared to counselling intervention (CG; advice on physical activity and dietary healthy behaviour) as a health centre intervention tool for the management of children’s obesity.

Secondary objectives are the evaluation of the effectiveness of the intervention changes in the following parameters at short, medium and long term following the intervention referred to as baseline:

a) Cardiovascular risk factors: Anthropometric parameters (BMI, BMI SD score, waist-size index and waist circumference), blood pressure (diastolic and systolic pressure) and blood tests (LDL cholesterol, HDL cholesterol, triglycerides, glucose, insulin, TSH and cortisol).

b) Physical condition evaluated by a physical fitness test.

c) Sedentary and physical activity behaviour and dietary intake.

d) Psychological aspects such as self-efficacy and self-concept.

e) Health related quality of life (HRQOL).

f) Cost-effectiveness of the intervention in relation to HRQOL.

## Methods/Design

### Trial design

The study design is a randomized controlled multicenter clinical trial over a period of 20 months (Figure 1) for overweight and obese children. They will be randomly allocated to study groups previous to participant’s recruitment. The study is children and family-based and includes an 8 month intervention of physical activity sessions for children, family sessions for parents, behaviour strategy sessions for children and parents, and weekend extra activities. Briefly, at least 100 obese children will be randomly allocated to either NP or CG. An assessment will be made before the intervention, 8 months later (at the end of the intervention), and 6 and 12 months of the follow-up period. All measurements will be taken at the same research unit and by trained researchers or HPU professionals blinded to the allocated study group.

**Figure 1 F1:**
[figure not shown]
Flow design.

After the follow-up period, the children in the control group will be offered to participate in the next season of the NP.

### Participants

Eligible participants will be children aged between 6 and 12 years old who are overweight or obese according the International Obesity Task Force Criteria (IOTF) defined by Cole et al. [23]. They are sedentary (less than 2 hours per week of physical activity outside school hours), live in or near the municipality of Lleida (Spain) and their healthcare paediatric unit (HCP) has previously accepted to cooperate in this study. In addition, at least one of the parents or guardians of the child must accept to actively participate in the study.

Exclusion criteria are: a) medical co-morbidities, such as Cushing disease, hypotiroidism, cardiovascular diseases or other serious chronic illnesses; b) use of medication that might have an effect on weight loss or adaptations to exertion; c) previous enrolment in other obesity treatment interventions; d) regular participation in physical exercise programs in the past 6 months.

### Randomization

On a first phase, professionals of the HCP in Lleida are informed of the purpose and the methodology of the study and are invited to participate in it. Sixteen HCPs accepted to cooperate in this study. Each HPU is responsible for the recruitment of participants and for the checking of their eligibility. Randomization will be centralized at the Primary Care Research Institute (IDIAP) Jordi Gol in Lleida. Each cooperating healthcare paediatric unit (HPU) will provide a random list of their patients/children fulfilling age and BMI SD scores inclusion criteria according to the data from their health clinical records. These eligible children will be randomly assigned to one of the study groups. Randomization will insure that patients are distributed to the 2 groups homogenously in terms of age and gender. Group homogeneity with regard to age will be assured by stratified randomization according to the age group: 6,7,8,9,10,11,12 years old (7 groups) in each HPU (16 HPU).

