### Recruitment strategy

Next, each HPU will phone/contact eligible families and will invite them to participate in the study. At that point participants will be informed about their study/case group. HPUs will recruit participants consecutively and on an alternate list mode basis, i.e. once they have recruited one eligible child from the intervention group list, they move on to recruit another participant from the CG list. Families of eligible children that accept to participate will be referred to their healthcare paediatric unit office for anin-depth explanation, followed by a medical assessment (basic exploration and blood test to check for inclusion and exclusion criteria). Children’s assent and written parental informed consent will be obtained from children who fulfil the inclusion criteria and with no exclusion criteria. The family will be finally included in the study.

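### Randomisation is said to ensure balance on age and gender, but nothing in the article controls gender, and the age stratification does not secure balance among the enrolled children

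*Protocol article*

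**What the plan says.** The Randomization section of the protocol article makes a firm promise: "Randomization will insure that patients are distributed to the 2 groups homogenously in terms of age and gender". It then explains how this is done for age: "Group homogeneity with regard to age will be assured by stratified randomization", with the strata given as "stratified randomization according to the age group: 6,7,8,9,10,11,12 years old (7 groups) in each HPU (16 HPU". No corresponding step is given for gender.

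The article describes in two ways who is randomised:

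- **Lists before recruitment.** Trial design says "They will be randomly allocated to study groups previous to participant’s recruitment". Randomization says each paediatric unit "will provide a random list of their patients/children fulfilling age and BMI SD scores inclusion criteria", and the children on these lists are allocated. The length of the lists is not given.
- **About 100 children.** Trial design also says "at least 100 obese children will be randomly allocated to either NP or CG".

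Under Recruitment strategy, families are approached after allocation and told their group: "HPUs will recruit participants consecutively and on an alternate list mode basis". Neither age nor gender is mentioned as governing who is approached next.

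The Statistical analysis plan section brings in multiple regression only if the groups turn out to differ on a relevant variable, after baseline significance tests. The logistic analysis of children who lower their BMI SD score is adjusted for baseline factors in any case.

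**The concern.** Balance on a factor is secured by stratifying, minimising or matching on it. The article guarantees balance on two factors and supplies a mechanism for one. For gender, the trial has only what any unstratified randomisation gives: balance on average, with chance gaps in a given trial.

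For age, the mechanism acts on the children who are randomised, while the analysis concerns those who enrol. If long lists are randomised and a few children per unit are then recruited from each arm's list, balance on the lists need not carry over. If instead only about 100 children are randomised, they are spread over more strata than there are children.

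Two things are at stake. A reader is told that the design has a property that it lacks. And because multiple regression depends on whether the groups happen to differ at baseline, an age or gender gap that the design does not prevent can decide which analysis is run. The Modifier variables section itself names pubertal development and demographic parameters as possible influences on the outcome.

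**Working it through.** The article prints neither a number of strata nor a balance figure, so there is no stated result to reproduce.

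**Inputs from the article.** Seven single-year age groups and 16 units (Randomization; "Sixteen HCPs accepted to cooperate in this study"); 50 children per arm, 100 in total (Sample size).

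**Assumptions.** Half the children are girls; ages and units are equally represented; lists hold 20, 40 or 70 children per unit, that is 320, 640 or 1,120 in all.

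**1. Gender**

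- SD of the between-arm difference in the proportion of girls: √(2 × 0.5 × 0.5 / 50) = 0.10.
- Normal approximation: a gap of 10 points or more is P(|Z| ≥ 1) = 0.32; a gap of 20 points or more is P(|Z| ≥ 2) = 0.046.
- Exact check: the difference in the number of girls is distributed as Bin(100, 0.5) − 50. Ten points is 5 children: 2 × P(Bin ≥ 55) = 0.37. Twenty points is 10 children: 2 × P(Bin ≥ 60) = 0.057.
- With 40% girls the SD is √(2 × 0.4 × 0.6 / 50) = 0.098, so the 50% assumption hardly matters.

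Stratifying by age and unit does not change this: in simulation the mean gap was about 8 points both with and without it.

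**2. Age**

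The measure is the difference in mean age between arms divided by the SD of age. Without stratification its SD is √(2/50) = 0.20, so it exceeds 0.2 in about P(|Z| > 1) = 32% of trials.

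*If lists are randomised:* 320/112 = 2.9 to 1,120/112 = 10 children per stratum. The simulation allocated each list in pairs within age group and unit, then drew three or four children per arm and unit at random, to reach 50 per arm.

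*If 100 children are randomised directly:* 7 × 16 = 112 strata and 100/112 = 0.89 children per stratum. Expected empty strata: 112 × (111/112)^100 ≈ 46. Chance that a child is alone in its stratum: (111/112)^99 = 0.41.

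| Scenario | Mean absolute age difference | Share of trials above 0.2 |
|---|---|---|
| No stratification | 0.16 | 34% |
| Lists of 320 to 1,120, alternating recruitment | 0.14 to 0.15 | 25% to 29% |
| 100 children in 112 strata, blocks of 2 | 0.11 | 15% |
| 100 children in 112 strata, blocks of 4 | 0.13 | 23% |

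Repeating the simulations with another seed gave 32%, 28% to 30%, 15% and 24%. Simulation error is thus up to about 3 points, and the order of the scenarios is unchanged.

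**3. Adding gender to the present strata**

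7 × 16 × 2 = 224 strata, or 100/224 = 0.45 enrolled children per stratum. Gender therefore cannot simply be added; the age groups have to be coarsened. Even two age bands × two genders × 16 units makes 64 strata, or 100/64 = 1.6 per stratum, which is why minimisation suits better than full crossing.

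**The case against.** The strongest objection is to setting 112 strata against 100 children. The detailed account in the Randomization and Recruitment strategy sections randomises record lists before anyone is approached, and these may be several times longer than 100. The strata then need not be sparse. This stands: the per-stratum figures apply only under the other wording in Trial design, and the two routes by which age balance weakens are alternatives that must not be added together.

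A reader might infer that the age stratification is no better than simple randomisation, or that age balance is not obtained at all. Neither is supported. Stratification reduced age imbalance in every scenario, modestly on the list reading and clearly if 100 children are randomised directly. What fails is the word ensure.

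It can also be said that the article does not state how each list is ordered, so recruitment might follow age order. That is possible, and a condensed article may omit it. The figure for the list reading therefore assumes unmatched recruitment. Alternation does keep the arm sizes close within each unit, which is a real merit.

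Finally, chance imbalance on age or gender does not in itself bias a randomised comparison, and the logistic analysis is already adjusted for baseline factors. Both points are right and limit the seriousness. They do not answer the gender promise, which the article makes itself and does not support, nor the conditional use of multiple regression.

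**Conclusion.** The point holds in limited form. The gender guarantee has no mechanism anywhere in the article; a gap of 10 points or more would arise in about a third of trials (32% by normal approximation, 37% exactly) and of 20 points or more in about 5% to 6%, assuming about half girls and 50 per arm.

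The age guarantee goes further than the design can deliver among enrolled children. On the list reading little of the balance carries over, given the assumed list sizes and recruitment without age matching; if about 100 children are randomised directly, balance is weakened but not lost.

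This does not make the treatment comparison invalid. It is an unsupported statement about the design, with a cheap remedy, and it should be corrected.

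**What to change.** 1. In the central randomisation at the research institute, replace the seven single-year groups with a few age bands, add gender, and keep the paediatric unit as a factor, for example by minimisation with a random element.
2. Prespecify age and gender as covariates in the primary BMI SD score model whatever imbalance is seen, in place of regression triggered by an observed difference. This is the more important step while allocation precedes recruitment, because gender balance on the lists would carry over to enrolled children only in part, as for age. It costs two covariates with 100 children.
3. At minimum, delete the statement that randomisation ensures gender balance and limit the age statement to the randomised lists. State whether the lists or about 100 children are randomised.

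The cost is some reprogramming of the central list and a few sentences of text, with no extra children or visits. Randomising only after consent would bring the balance to the enrolled children, but it reverses the present order of allocation, contact and consent at the units. That is a larger change, to be weighed separately.

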### Recruitment strategy

Next, each HPU will phone/contact eligible families and will invite them to participate in the study. At that point participants will be informed about their study/case group. HPUs will recruit participants consecutively and on an alternate list mode basis, i.e. once they have recruited one eligible child from the intervention group list, they move on to recruit another participant from the CG list. Families of eligible children that accept to participate will be referred to their healthcare paediatric unit office for anin-depth explanation, followed by a medical assessment (basic exploration and blood test to check for inclusion and exclusion criteria). Children’s assent and written parental informed consent will be obtained from children who fulfil the inclusion criteria and with no exclusion criteria. The family will be finally included in the study.

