### Statistical methods

#### Management and data analysis

All data will be recorded in an electronic data sheet. Two samples will be drawn; one by intention-to-treat (ITT) and another per protocol (PPT). The ITT sample will get-together all participants assigned to each group independently of whether they complete or not the entire protocol. The PPT sample will only assemble the participants who complete the entire protocol. The analysis of the results will be carried out according to the statistical analysis plan.

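### Allocation is not concealed at enrolment: children are randomised from record lists, and the arm is disclosed at the invitation call, before the remaining eligibility checks and consent.

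*Protocol article*

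**What the plan says.** The order of events is spread over three sections of the protocol article.

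- **Trial design** puts allocation first: "They will be randomly allocated to study groups previous to participant’s recruitment".
- **Randomization** describes the source of the children for each healthcare paediatric unit (HPU), saying that it "will provide a random list of their patients/children fulfilling age and BMI SD scores inclusion criteria according to the data from their health clinical records". The next step is given as follows: "These eligible children will be randomly assigned to one of the study groups". It also says "Randomization will be centralized at the Primary Care Research Institute (IDIAP) Jordi Gol in Lleida", and makes the HPU responsible both for recruiting and for checking eligibility.
- **Recruitment strategy** has the HPU phone the listed families and invite them. On that call, "At that point participants will be informed about their study/case group". Recruitment is consecutive and alternates between two lists: "once they have recruited one eligible child from the intervention group list, they move on to recruit another participant from the CG list". Families who accept then attend for the detailed explanation and a medical assessment with blood test against the inclusion and exclusion criteria. Assent and parental consent follow, and inclusion is the last step.

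**Management and data analysis** defines the main sample: "The ITT sample will get-together all participants assigned to each group independently of whether they complete or not the entire protocol". **Sample size** sets a target of 50 per group.

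**The concern.** Concealment means that nobody who decides whether a child enters the trial knows which arm the child would enter. Here the unit staff know it when they invite and when they judge eligibility, and the family knows it when it accepts or refuses. Refusals and screen failures therefore come after randomisation and can depend on the arm.

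The two offers are very different. Nereu asks for three one-hour child sessions a week over eight months and a weekly parent session. Counselling asks for a short monthly visit. Families willing to take on Nereu may be more able or more motivated than families willing to take on counselling, and such traits may themselves predict change in BMI SD score. Randomising the list makes the listed groups comparable. It does not make the enrolled groups comparable. An intention-to-treat analysis cannot restore what is lost before consent, because those children supply no outcome.

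**Working it through.** **Step 1. Sequence and knowledge of the arm**

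| Step | Section | Arm known to recruiter? | Arm known to family? |
|---|---|---|---|
| 1. List drawn from records (age, BMI SD score) | Randomization | no | no |
| 2. Listed children randomised centrally | Randomization; Trial design | – | – |
| 3. HPU phones from two arm-specific lists | Recruitment strategy | yes | told on this call |
| 4. Family accepts or declines | Recruitment strategy | yes | yes |
| 5. Medical assessment, blood test, inclusion and exclusion check | Recruitment strategy | yes | yes |
| 6. Assent, consent, inclusion | Recruitment strategy | yes | yes |

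The criteria under Participants that the list does not screen, and that are therefore settled after step 2, are sedentary status, active participation by a parent, and the exclusions. Some of these involve judgement.

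**Step 2. Difference in burden**

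- Nereu: 90 child sessions × 60 min = 90 h, and 21 parent sessions × 60 min = 21 h.
- Counselling: 8 × 10 min = 80 min, or about 1.3 h.

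Unequal acceptance is therefore plausible. The documents give no acceptance rates.

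**Step 3. Illustration of size (all selection inputs are assumed)**

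Let M be standard normal motivation and e independent standard normal noise. A family accepts if (M + e)/√2 exceeds the cut-off that gives acceptance proportion p in its arm. Let λ(p) = φ(z)/p, where z is the upper-p cut-off of the standard normal. Then mean M among acceptors is λ(p)/√2, and with correlation ρ between M and outcome

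bias (SD) = ρ × [λ(p_Nereu) − λ(p_counselling)] / √2.

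Values: λ(0.30) = 1.159, λ(0.50) = 0.798, λ(0.60) = 0.644, λ(0.80) = 0.350.

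With 50 enrolled and the planned 20% dropout, 50 × 0.8 = 40 per arm, so SE = √(2/40) = 0.224 SD. Type I error = Φ(bias/SE − 1.96) + Φ(−bias/SE − 1.96).

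| Acceptance, Nereu / counselling | ρ | Bias (SD) | Share of planned 0.60 | Type I error |
|---|---|---|---|---|
| 50% / 60% | 0.1 | 0.011 | 2% | 5.0% |
| 50% / 60% | 0.3 | 0.033 | 5% | 5.2% |
| 30% / 60% | 0.3 | 0.109 | 18% | 7.8% |
| 30% / 80% | 0.1 | 0.057 | 10% | 5.8% |
| 30% / 80% | 0.3 | 0.172 | 29% | 12.0% |
| equal, common threshold | any | 0 | 0% | 5.0% |

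Check of the fifth row: 0.3 × (1.159 − 0.350)/1.414 = 0.172; 0.172/0.224 = 0.77; Φ(−1.19) + Φ(−2.73) ≈ 0.120.

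Across the assumed ranges (30-50% against 60-80%, ρ 0.1-0.3) the bias runs from 0.01 to 0.17 SD and the type I error from 5.0% to 12.0%. If acceptance were lower in counselling than in Nereu, the sign would reverse. The result also depends on the model: if acceptance is driven wholly by the trait that is correlated with outcome, the factor 1/√2 drops out and the bias is 1.41 times as large. Arm-aware eligibility judgement by the recruiter is not modelled.

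**The case against.** Several points on the other side have weight.

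- **Some eligibility is settled beforehand.** Age and BMI SD score are screened before randomisation. This stands: only the remaining criteria are checked with the arm known.
- **Generation is central and recruitment is consecutive.** Both stand. Central generation protects the sequence, and consecutive calling narrows the room to pick families. Neither hides the arm from the person judging eligibility or from the family.
- **Direction is not established.** A reader might infer that Nereu must end up with the more motivated families. The documents do not show this. Nereu's weekend outings may raise its acceptance, the later offer of Nereu to the control group may change who accepts counselling, and some families may find eight short meetings too little. Only the possibility of unequal acceptance is supported.
- **Replacement and reporting.** A reader might infer that refusals are replaced and concealed. The text states alternation and a target of 50 per group, and the Discussion allows a wider search for children if needed. It does not say that decliners go unreported. The article says its methods agree with CONSORT, and the flow figure is not available here.
- **The intention-to-treat definition.** A reader might infer that the plan excludes decliners. It does not say so, and read literally the definition could cover every child assigned. The practical difficulty remains, because decliners give no consent and no outcome data.
- **Mitigation.** Outcome measurement is blinded, socio-economic status and self-efficacy are recorded, and adjustment for baseline factors is planned. These help with measurement bias and measured imbalance, but not with unmeasured motivation or capacity.

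**Conclusion.** The point holds as a flaw of enrolment. Allocation is not concealed from the recruiter or the family at the time of invitation, the remaining eligibility checks and consent, and nothing elsewhere in the protocol restores concealment. Alternating between lists can balance numbers without restoring comparability.

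The consequence is a risk of selection bias whose size and direction cannot be derived from the documents. The illustrated range runs from negligible to more than a quarter of the planned effect of 0.60. It rests wholly on the assumed acceptance rates, the assumed correlation and the chosen model, so it should not be read as an estimate. The case for change does not depend on it: the order of steps is stated explicitly, and its effect cannot be undone once children are enrolled.

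**What to change.** Change the order of steps:

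1. The HPU invites families to a trial of two programmes without naming an arm.
2. It completes all eligibility checks, assent and consent, and the baseline measurements.
3. It then obtains the child's allocation from the central office at IDIAP, which already runs the randomisation.
4. The two arm-specific lists and alternate recruitment are dropped.
5. Intention-to-treat is defined as all children randomised at step 3, analysed in the arm assigned.

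The cost is a protocol amendment and a new invitation script. Some families may withdraw on learning their arm. Under this order they stay in the intention-to-treat denominator with baseline data, so any imbalance in withdrawal can be seen and examined.
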